### Assessment

Each participant will be assessed by a blinded assessor who is unaware of group allocation. Assessors will attend training days in order to standardise the measurements.

Assessments will be carried out at baseline (week 1), post-intervention (week 12) and at follow-up (week 24). The following outcome measures will be used for all three assessments: Multiple Sclerosis Impact Scale 29 version 2 (MSIS), Modified Fatigue Impact Scale (MFIS), six minute walk test (6MWT), physiological cost index (PCI), and hand held dynamometry (HHD). In addition the Berg Balance Scale (BBS) and the Modified Ashworth Scale (MAS) will be used for strand B. As equipment for PCI and HHD are not available to all assessors some participants will not have these measures recorded. The more physically demanding outcome measures were separated to avoid fatigue and so the order of testing for strand A was 6MWT including PCI, MSIS, HHD, MFIS. For strand B it was 6MWT including PCI, MSIS, BBS, MFIS, MAS, HHD

A standardised assessment at baseline considered the participants suitability for exercise and measured confounding variables such as level of sensory loss, coordination deficits etc.

#### The 6 Minute Walk Test including Physiological Cost Index

In the 6MWT, the participants will be asked to walk for a period of six minutes and the distance walked is recorded. Paltamaa et al[25] found that the 6MWT is highly reliable in people with mild to moderate MS (EDSS 2–6.5) and Marrie and Goldman[26] validated the 6MWT as an outcome measure for PwMS. Subjects will be instructed to walk as quickly and safely as possible as recommended by Fry and Pfalzer[27].

During the 6MWT the heart rate of each participant will be recorded in order to calculate the PCI. The PCI is a measure of energy is measured by calculating the heart rate during locomotion minus the resting hear rate divided by the speed of walking[28].

The exercising heart rate will be measured by a polar monitor (a strap around the chest and a watch). The resting heart rate will be measured by the patient first thing in the morning using the carotid pulse in the neck.

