### Interventions

The physiotherapy interventions for strands A and B are standardised and based on the latest evidence for practice in order to allow reproduction of the programmes. The Yoga and Fitness Instructor interventions are not specified, in order to represent normal practice, but are well documented to allow comparison later.

To ensure standardisation of physiotherapy interventions, training for those physiotherapists delivering the programmes will be held on three occasions, supporting documentation will be provided and follow up advice and information for deliverers was supplied as necessary by e-mail and telephone. The content of the interventions for both strands is described below. The attendance and participation of each study participant will be documented on a weekly basis.

The control groups in both strands will not receive any intervention for the 12 weeks and were told to continue with their normal routine. Once the control period is over participants will receive the treatment of their choice but the response to this will not be assessed as part of this trial.

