#### Strand A

##### Intervention 1 – Physiotherapy led strength and aerobic training

Participants will attend an hour long circuit class once a week for ten weeks. This will be a circuit style class consisting of Sit to stand/squat, bridging, resisted shoulder flexion, walking/bike, resisted elbow flexion, lunges or resisted knee extension, hip extension, calf raises. All exercises will be completed at 50 – 80% of the participants' one-repetition-maximum and the load will be increased by 2 – 5% when twelve repetitions are easily achieved. The aim is for the participant to be failing on the last repetition. If the next available load is higher than 2 – 5% (such as going from 1 kg to 2 kg in resisted shoulder flexion) the participant can increase the repetitions so that they are still failing to achieve full range on motion on the last one. The primary aim is to achieve "overload" of the muscle to achieve gains in strength. Participants will be educated about the overload principle and that delayed onset of muscle soreness is a normal phenomenon. After five weeks of attending the class, participants will be advised to complete a second hour of strengthening themselves at home.

A second component of the class will be advice regarding aerobic exercise. In the first class, 10 minutes will be devoted to formally explaining aerobic exercise, Uhtoff's phenomenon (whereby increasing heat in people with MS can temporarily exacerbate symptoms) and the evidence supporting aerobic activity.

Each participant will be given a target heart rate. This will be calculated using the Karvonen formula which is: Target Heart Rate = Resting Heart Rate + 65% (Maximum Heart Rate).

The participants will be advised in the initial assessment how to get their resting heart rate, by feeling their carotid pulse for 30 seconds first thing on waking. The first beat they feel will be zero. As a maximal exercise test will not be conducted, each participant's age predicted maximum heart rate will be used as the target HR (i.e. 220 – age). If they are unable to detect a pulse they will aim to exercise at a Rate of Perceived Exertion level of 11 – 14.

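### The physiological cost index subtracts a self-counted morning pulse from a chest-monitor walking rate: avoidable measurement error in a minor outcome, with a cheap remedy

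*Protocol article*

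**What the plan says.** The section on the 6 Minute Walk Test defines the index as "heart rate during locomotion minus the resting hear rate divided by the speed of walking". For the walking rate it says "The exercising heart rate will be measured by a polar monitor (a strap around the chest and a watch". For the resting rate it says "The resting heart rate will be measured by the patient first thing in the morning using the carotid pulse in the neck".

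The Assessment section lists the index among the measures taken at baseline, week 12 and week 24, and says "Each participant will be assessed by a blinded assessor who is unaware of group allocation". It also accepts that the index will be missing for some participants because not every assessor has the equipment.

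More detail on the self-taken pulse stands only under Strand A, Intervention 1 (physiotherapy-led training), where it serves the target heart rate. There, participants learn at the initial assessment to obtain the resting rate "by feeling their carotid pulse for 30 seconds first thing on waking", with the rule "The first beat they feel will be zero". A fallback to perceived exertion follows for the case "If they are unable to detect a pulse". The same arm is asked to check its pulse every ten minutes during independent aerobic sessions.

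The trial is single blind, and only the assessor is described as blinded. Under Interventions, control participants receive nothing for 12 weeks and "were told to continue with their normal routine".

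**The concern.** The numerator of the index is a difference between two heart rates, so an error in either passes straight into it. Here one rate is read from an instrument at the assessment. The other is palpated by the participant earlier in the day, with no assessor check or repeat reading described. Three consequences follow, and they are not equally certain.

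- **Measurement error.** Different instrument, observer and time add error that one device at one visit would largely avoid. This follows directly from the text.
- **Reporting bias.** The resting rate comes from someone who is not blinded, although the outcome is listed as part of a blinded assessment. This is a possibility, and it depends on when the pulse is taken.
- **Missing values.** The article expects that some people will not find their pulse. The fallback it gives sets exercise intensity and supplies no resting rate for the index. Whether values are lost depends on whether the same method feeds the index.

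**Working it through.** The article gives no value of the index, of heart rate or of walking speed, so there is no stated figure to reproduce. The sizes below use assumed inputs.

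**Inputs**
- From the article: index = (walking rate − resting rate) / speed; six-minute walk; a 30-second count (Strand A physiotherapy section; its use for the index is an inference).
- Assumed: 400 m walked, so 400/6 = 66.7 m/min; 150 m walked, plausible in Strand B, so 150/6 = 25 m/min; a constant gap of 10 beats/min between waking and pre-walk rest; a speed gain of 5-10%.

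**Step 1: counting error.** A 30-second count has to be doubled to give beats/min (implied, not stated), so one beat miscounted is 2 beats/min. Shift in the index = error / speed:
- 2 / 66.7 = 0.03 beats/m
- 2 / 25 = 0.08 beats/m

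An overcount lowers the index and an undercount raises it. The same arithmetic gives the effect of a mean error that differs between arms: a 2 beats/min difference would produce a false between-arm difference of 0.03 or 0.08 beats/m. The article does not show that such a difference exists. It does state pulse-taking practice for the Strand A physiotherapy arm and for no other arm, so accuracy could differ by arm.

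**Step 2: a constant gap between waking and pre-walk rest.** At one time point the gap c shifts the level by c / speed:
- 10 / 66.7 = 0.15 beats/m
- 10 / 25 = 0.40 beats/m

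This shift applies to every arm and every visit. In a change score only the part due to a change in speed remains. With a proportional gain g, the spurious change is c / (v(1+g)) − c / v:

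| Baseline speed v | g = 5% | g = 10% |
|---|---|---|
| 66.7 m/min | 0.1429 − 0.1500 = −0.007 | 0.1364 − 0.1500 = −0.014 |
| 25 m/min | 0.3810 − 0.4000 = −0.019 | 0.3636 − 0.4000 = −0.036 |

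The residual is g/(1+g) of the level shift, that is 0.05/1.05 = 1/21 to 0.10/1.10 = 1/11 of it.

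**Step 3: does the text offset the mismatch?** Assessor training is mentioned, but it standardises what assessors do, and the resting rate is taken outside the assessment. The monitor has to be fitted for the walk wherever the index is measured, so reading rest from it needs no new equipment.

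**Step 4: what the text leaves open.** It does not say whether the resting pulse is retaken at weeks 12 and 24, or when participants learn their allocation relative to baseline. If the baseline pulse is reused, knowledge of allocation matters much less and its error behaves like the constant gap in Step 2, but any change in resting rate is missed.

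**The case against.** The strongest reply has five parts.

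1. The 30-second count and the undetectable-pulse case belong to the exercise prescription of one arm. The section on the index states neither, and a fallback may exist in assessor materials that a condensed article does not carry. This stands, so the miscount figures and the missing values are conditional.
2. Bias is not demonstrated. Without knowing whether the pulse is retaken, or when allocation becomes known, neither its direction nor its size can be derived. This stands. Unblinded participants also complete the MSIS-29 and the fatigue scale, so the index is not the trial's main exposure to reporting bias.
3. A reader might take the 0.15 and 0.40 beats/m of Step 2, or the remark that a 10-beat gap is 25% of the index at an assumed 40 beats/min rise (10/40), as the distortion of the trial's comparisons. The documents do not support that. These are shifts in level common to all arms, and most of the shift cancels.
4. A reader might also infer that values are lost mainly among people with more sensory or hand impairment. The article gives no number unable to find a pulse and no link to impairment. The loss it does state comes from equipment, which the fix leaves untouched.
5. A waking rate is a coherent definition of rest, and a rate taken just before a walk can carry anticipation effects. This is a fair cost of the change. It does not answer the mismatch of instrument and observer.

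What remains is the mismatch itself, which the article states explicitly and nothing in it offsets.

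**Conclusion.** The point holds in limited form. The index combines a monitor reading with a self-counted pulse taken at another time by an unblinded participant. That adds measurement error which could easily be avoided, and it leaves reporting bias and missing values as possibilities.

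The plausible sizes are small to moderate: 0.03-0.08 beats/m for a one-beat miscount, if the 30-second method applies, and about 0.007-0.036 beats/m of spurious change from a constant 10-beat gap. All rest on the assumed distances, gap and speed gain.

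The index is not the primary outcome, is not among the secondary outcomes named in the abstract, and does not enter the sample size. The trial's main conclusion is therefore unaffected, and the priority is low.

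**What to change.** Wherever the index is measured, have the blinded assessor record the resting rate from the same chest monitor after a fixed seated rest (for example five minutes) immediately before the walk, at weeks 1, 12 and 24. Use that rate in the index. The home waking pulse can stay for its other stated use without entering the outcome.

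This removes the self-count, the unblinded reporter and any loss from an undetected pulse. It does not recover values missing because an assessor lacks the equipment.

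The cost is a few minutes per visit, possible anticipation effects on the pre-walk rate, and less direct comparability with studies that use a waking rate.

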#### The Multiple Sclerosis Impact Scale 29 (MSIS-29)

The MSIS – 29 is a measure of the physical and psychological impact of MS from the patient's perspective. The MSIS – 29 was found to have good psychometric properties in an Irish Community dwelling population of PwMS[29]. The MSIS – 29 is an easy instrument to administer, taking approximately 5 minutes to complete. All estimates of reliability using Cronbach's alpha were in excess of the recommended 0.80. The convergent and divergent validity is established and it has moderate sensitivity to change. It has been shown to have better responsiveness compared to SF – 36 and the FAMs which also consider quality of life[30]. High scores on the MSIS-29 indicate greater impact of MS.

#### The Berg Balance Scale (BBS)

The BBS is a clinical scale that evaluates balance in sitting and standing and rates performance from 0 (cannot perform) to 4 (normal performance). The scale has fifteen items that explore the ability to sit, stand, lean, turn and maintain the upright position on one leg. The BBS has been validated for use in people with multiple Sclerosis[31]. It was found to have good concurrent validity and a cut off score of 44 (out of 56) was established as a criterion to identify PwMS who have a high risk of falls. The reliability of the BBS has also been examined in PwMS[32,33]. It was found to have high test retest and interrater reliability, both having intraclass correlation coefficients (ICCs) of 0.96. The BBS is widely used by physiotherapists and takes approximately 15 minutes to complete. It is also used in other studies evaluating interventions in PwMS[34], therefore, making it possible to compare results to other studies.

#### The Modified Fatigue Impact Scale (MFIS)

The MFIS is a structured self report questionnaire. The subscales are how fatigue relates to physical, cognitive and psychosocial aspects functioning. This version has a Cronbachs alpha of .81 indicating good reliability[35]. A recent review of the literature[36] suggested that the MFIS may have greater sensitivity to change than the Fatigue Severity Score. Administration time is approximately 5 to 10 minutes.

#### The Modified Ashworth Scale

The Modified Ashworth Scale (MAS) is a 6 point ordinal scale that is used to measure spasticity. It is designed to grade the level of resistance encountered during passive movement and scores range from 0 (no increase in muscle tone) to 5 (rigidity of the affected limb). It is widely used in clinical practice and has been shown to have good to excellent interrater and intrarater reliability in people with spasticity post stroke[37]. Its validity has been determined with the use of electromyographic recordings of muscle activity in patients with spinal cord injury [38-40]. It has also been used in other studies evaluating interventions for PwMS[41], making comparisons between results possible.

#### Handheld Dynamometry

Handheld dynamometry has been found to be more reliable than manual muscle testing (REF). The standardised positions described by Bohannon[42,43] will be used to measure strength in both the upper limbs and the lower limbs.

### Sample size calculations

#### Strand A

Based on a pilot study and the MSIS physical component scores then a sample size of 60 in each group will be sufficient to show a similar probability (0.329) that an observation after intervention will be less than before intervention as in the pilot study (mean before intervention 62.4, after intervention 53.6). This is based on using the Wilcoxon Signed Rank Test, significance level 0.05 and a power of 90%.

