## Methods and design

### Design

This will be a multi-centre, prospective, single blinded, block randomised controlled trial. Participants will be stratified according to mobility level using the mobility section of the Guys Neurological Disability Scale[24]. Those who score 0, 1 or 2 are stratified to stand A, those scoring 3 and 4 to strand B. For each strand blocks of subjects will be randomised to one of the interventions or to the control group.

Strand A will concern individuals with MS who walk independently or use one stick to walk outside. The objective is to compare the immediate and long term effect of yoga, physiotherapy led exercise class, fitness instructor led exercise class to a control group who don't change their exercise habits.

Strand B will concern individuals with MS who walk with bilateral support or a rollator, they may use a wheelchair for longer distance outdoors. The objective is to compare the immediate and long term effect of 1:1 Physiotherapist led intervention, group intervention led by Physiotherapist, or group yoga intervention to a control group who don't change their exercise habits.

The study protocol was approved by 10 regional ethics committees in the Republic of Ireland

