#### Strand B

Based on a pilot study and the MSIS physical and psychological component scores then a sample size of 22 in each group will be sufficient to show a similar probability (0.217) that an observation after intervention will be less than before intervention as in the pilot study (mean before intervention 23.0, after intervention 18.8). This is based on using the Wilcoxon Signed Rank Test, significance level 0.05 and a power of 90%.

As parametric tests require less subjects for the same power these numbers should be sufficient even if these tests are used instead of the non-parametric tests given above.

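### The 90% power is stated for a before-after change with a paired test; it reaches the comparison with control only under assumptions the protocol does not state, and the named test does not match the numbers.

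*Protocol article*

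**What the plan says.** Under Sample size calculations, Strand A: "a sample size of 60 in each group will be sufficient to show a similar probability (0.329"), this being the chance that a score after intervention is below the score before it. The pilot values are "mean before intervention 62.4, after intervention 53.6". The basis is given as: "This is based on using the Wilcoxon Signed Rank Test, significance level 0.05 and a power of 90" (per cent).

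Strand B has the same form: "a sample size of 22 in each group will be sufficient to show a similar probability (0.217"), with "mean before intervention 23.0, after intervention 18.8" and the same test, level and power. The section closes: "As parametric tests require less subjects for the same power these numbers should be sufficient even if these tests are used instead".

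The Design section sets the Strand A objective as to "compare the immediate and long term effect of yoga, physiotherapy led exercise class, fitness instructor led exercise class to a control group". Strand B has a parallel objective with its own three interventions.

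The Statistical Analyses section uses the signed rank test for change before to after. Between groups it uses Mann-Whitney U, or repeated measures ANOVA if the data are near normal. The abstract's Discussion says that both change in each group and differences between groups will be analysed.

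**The concern.** A signed rank test on before-after scores asks whether one arm changed. It cannot separate a treatment effect from time, expectation or regression to the mean, which is what the control arm is for. A contrast between arms carries the sampling error of two groups and counts only the improvement beyond that in controls. The sample size section gives no between-arm difference, no expected change in controls and no SD, so its 90% is not tied to the comparison named as the objective.

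The closing sentence about parametric tests does not bridge the gap. The relative efficiency of a parametric test against the signed rank test concerns the same within-arm question. It says nothing about moving to a comparison between groups.

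At stake is how a null result is read. If intervention and control do not differ significantly, a reader who relies on the 90% may take this as good evidence of no effect. Depending on what the pilot probabilities mean and how controls behave, the trial may have had much less power than that.

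**Working it through.** **Inputs from the article.** p = 0.329 and n = 60 per group (Strand A); p = 0.217 and n = 22 per group (Strand B); level 0.05; power 90%. Sidedness is not stated; two-sided reproduces the sizes below and one-sided does not (49 and 18). K = (1.960 + 1.282)² = 10.507.

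**Reproducing 60 and 22.**
- Noether, two samples (Mann-Whitney), n per group = K / [6(p − 0.5)²]. A: 10.507 / (6 × 0.02924) = 59.9, so 60. B: 10.507 / (6 × 0.08009) = 21.9, so 22. Both are exact.
- Noether, signed rank, n = K / [3(p − 0.5)²]. A: 119.8, so 120. B: 43.7, so 44. Neither matches.
- Signed rank on normal paired differences. The standardised change is dz = Φ⁻¹(1 − p) = 0.443 (A) and 0.782 (B). With a small-sample term, n = (K/dz² + 1.96²/2) × π/3, which gives 58.2, so 59, and 20.0, so 20. This is close but not equal.

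The numbers thus look like a two-group formula fed with a before-after probability, with a paired test named beside it. All of these depend only on the distance of p from 0.5. So it does not affect n that both probabilities are below 0.5 although the pilot means fall (0.671 and 0.783 would fit the described direction).

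**Between-arm power at 60 and 22 per arm.** The article supplies no SD or control change, so what follows rests on assumptions: normal data, equal SDs, two-sided 0.05, and controls improving by a fraction f of the pilot change.
- *Paired reading*: p refers to within-person differences and arms are compared on change, so d = dz(1 − f).
- *Independent-sample reading*: p compares two separate samples and arms are compared on post scores, so d = √2 · dz(1 − f), which is 0.626 (A) and 1.106 (B) at f = 0.
- *Baseline adjustment* at an assumed correlation r of 0.5 to 0.8 divides d by √[(1 + r)/2] on the paired reading and by √(1 − r²) on the other.

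| Reading | Controls improve by | Unadjusted, A / B | Baseline-adjusted, A / B |
|---|---|---|---|
| Paired | none | 67% / 72% | 72-79% / 76-83% |
| Paired | a quarter | 44% / 48% | 48-55% / 52-59% |
| Paired | a half | 23% / 25% | 24-28% / 27-31% |
| Independent | none | 90-93% / 90-95% | 98% or more / 98% or more |
| Independent | a quarter | 69-72% / 72-77% | 84-99% / 87-99% |
| Independent | a half | 38-40% / 42-43% | 50-81% / 54-85% |

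The paired figures are from the noncentral t; simulated Mann-Whitney power is 2 to 3 points lower (65% / 69% with unchanged controls). The unadjusted independent figures run from Noether's approximation to the noncentral t. On the paired reading with unchanged controls, 90% unadjusted power would need about 108-113 (A) and 35-36 (B) per arm.

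The same table covers two active arms: the rows for a half apply where the arms differ by half the pilot change.

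**The case against.** The strongest reply is that 60 and 22 match a two-sample calculation exactly, so the authors may well have computed Mann-Whitney power and misnamed the test. On that reading the 90% does carry over to intervention versus an unchanged control, and baseline adjustment would raise it. This stands, and it rules out the stronger statement a reader might infer, that the 90% has no bearing on the between-arm comparison. What remains is that the effect is still defined as after versus before, the text names another test, and the assumption of unchanged controls is nowhere stated.

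Second, the article does plan within-arm signed rank tests, so the 90% describes a real planned analysis. That is correct, but it is not the randomised comparison.

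Third, the objective is each intervention versus control, and no power is claimed for comparing active arms. This also stands. That comparison comes from the Discussion's broader question of which intervention should be delivered, so the article need only say that it is not powered.

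A reader might also infer that the pilot had no control group. The article says only that there was a pilot study and gives no control figure, so this cannot be asserted. Nor does the article say that the repeated measures ANOVA will test a group-by-time interaction; it mentions only differences between groups and over time.

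Finally, an article condenses a fuller plan. But the power statement here is made explicitly, and the mismatch lies in what it states, not in what it omits.

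**Conclusion.** The point holds in a limited form. The stated 90% belongs to a before-after effect and a paired test, and the named test does not produce the stated sizes by the formula that fits them exactly. For intervention versus control, the 90% is supported only if the pilot probabilities are independent-sample ones and controls do not change.

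Outside those conditions unadjusted power may be 67% / 72% (A / B; paired reading, unchanged controls), about 70-77% (independent reading, controls improving by a quarter), or as low as 23% / 25% (paired reading, controls improving by half). Baseline adjustment recovers part of this, and on the independent reading much of it.

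The mismatch itself is certain from the text. The size is not: normality, the control changes of a quarter and a half, and the correlations of 0.5 to 0.8 are all assumptions from outside the article. It would therefore go too far to conclude that the trial is underpowered; the article does not show which case applies. Allocation by whole blocks is a separate issue and is not in these figures.

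**What to change.** In the sample size section, for both strands:
- Restate power at the planned 60 and 22 per arm for each intervention versus control on week 12 MSIS adjusted for baseline. Take the SD from the pilot data, state an explicit control-arm change, and show the result as a range over plausible values.
- Say whether 0.329 and 0.217 are paired or independent-sample probabilities, name the test that was actually used to obtain 60 and 22, and correct the direction of the probabilities if it is reversed.
- State that comparisons between active arms are not powered and will be reported with confidence intervals.
- Delete the sentence on parametric tests needing fewer subjects.

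The cost is two rewritten paragraphs and probably a less favourable stated power. Enrolment and trial conduct do not change.

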### Statistical Analyses

All measures will be summarised and tested for normality. If variables are non-normal then Wilcoxon Signed Rank tests will be used to test for differences before and after interventions and Mann-Whitney U tests will be used to test for differences between groups before and after interventions. If the variables are reasonably normally distributed then repeated measures ANOVA will be carried out to test for differences between groups and over time. Suitable plots will be used to demonstrate the changes found.

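### The 60 and 22 per group match a two-sample rank-sum formula, not the Wilcoxon Signed Rank Test named as their source, so the 90% power is not shown for the named test

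*Protocol article*

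**What the plan says.** Under Sample size calculations, Strand A, the protocol article says that "a sample size of 60 in each group will be sufficient to show a similar probability (0.329"), and defines that probability as the one "that an observation after intervention will be less than before intervention as in the pilot study". The pilot figures given are "mean before intervention 62.4, after intervention 53.6". The test is named in the next sentence: "This is based on using the Wilcoxon Signed Rank Test, significance level 0.05 and a power of 90" per cent.

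Strand B follows the same pattern: "a sample size of 22 in each group will be sufficient to show a similar probability (0.217"), with pilot means of 23.0 before and 18.8 after, and again "This is based on using the Wilcoxon Signed Rank Test" at the same significance level and power.

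Neither paragraph gives a standard deviation of change, a within-person correlation, a distribution for the differences, or the sidedness of the test.

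The Statistical Analyses section keeps the two rank tests apart. For non-normal variables, the signed rank test is for change from before to after, and "Mann-Whitney U tests will be used to test for differences between groups before and after interventions".

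**The concern.** The signed rank test uses paired differences within one group. The Mann-Whitney test compares two independent groups. They have different sample size formulas and, in this plan, answer different questions. If the sizes come from one formula and the text names the other, the only power statement in the article is attached to the wrong test.

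Two things are at stake. A reader cannot tell which comparison has 90% power. And because a rank-sum size looks like a between-group size, a reader may take 90% as the power against control, although the effect that was entered is a change from before to after in a pilot.

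**Working it through.** **Inputs from the document.** Probability p = 0.329 and n = 60 per group (Strand A); p = 0.217 and n = 22 per group (Strand B); significance level 0.05; power 90%. **Assumption.** The test is two-sided; the article does not say. Then (1.960 + 1.2816)² = 10.507.

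**1. Reproducing the plan's figures: two-sample rank-sum (Noether), equal groups.** n per group = 10.507 / [6(p − 0.5)²].
- Strand A: 10.507 / (6 × 0.171²) = 10.507 / 0.17545 = 59.89, rounded up to 60.
- Strand B: 10.507 / (6 × 0.283²) = 10.507 / 0.48053 = 21.87, rounded up to 22.

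Both match exactly. The formula's power at 60 and 22 is 90.1% and 90.2%. One-sided 0.05 gives 49 and 18, which do not match. In Strand A only values of p from about 0.328 to 0.329 round up to 60, so a chance match in both strands is unlikely.

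**2. Closed-form formulas for paired tests, same inputs.**

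| Route | Strand A | Strand B |
|---|---|---|
| Signed rank (Noether), p used as the Walsh-average probability: 10.507 / [3(p − 0.5)²] | 119.8 → 120 | 43.7 → 44 |
| Sign test: 10.507 / [4(p − 0.5)²] | 89.8 → 90 | 32.8 → 33 |
| Signed rank (Noether), p read as the probability that a paired difference is negative, normal differences | 63.8 → 64 | 26.2 → 27 |

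The Walsh-average probability is the chance that the average of two participants' differences falls on one side of zero. For the third row, the standardised shifts implied by p are 0.443 and 0.782. The corresponding Walsh-average probabilities are 0.266 and 0.134, and these go into the first-row formula. None of the three routes gives 60 and 22.

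**3. Signed-rank power at the stated sizes, by reading of p.**

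| Reading of p | n = 60 | n = 22 |
|---|---|---|
| Probability for a paired difference, normal differences (simulated) | 91% | 93% |
| Same, t with 3 df | 82% | 85% |
| Same, Laplace | 75% | 83% |
| Same, uniform | 98% | 98% |
| From treating before and after scores as independent normal samples, true within-person correlation 0.5 (simulated) | over 99% | over 99% |
| Walsh-average probability (Noether) | 63% | 63% |

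The distributions and the correlation are assumptions; the document gives none.

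**4. Direction.** The text makes 0.329 and 0.217 the probability that the after score is the lower one. Both are below 0.5, so most scores would not fall. The pilot means do fall, by 62.4 − 53.6 = 8.8 and 23.0 − 18.8 = 4.2. The likeliest explanation is a reversed label. The sizes are unaffected, because each formula depends on p only through (p − 0.5)².

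**The case against.** The strongest reply is that the named test may have the stated power anyway. If p is the probability that a paired difference is negative, which is the plainest reading of the text, and differences are normal, simulation gives 91% and 93% at 60 and 22, and about 59 and 20 to 21 pairs would be enough. The 64 and 27 in the working come from an approximation that the simulation shows to be conservative here, so they do not prove a shortfall. This stands, and it rules out a claim that the paired test is underpowered. It does not rescue the attribution: that route needs a distribution the article never states, and it does not give both integers, whereas the rank-sum formula does so from the printed inputs and two-sidedness alone.

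Three stronger readings are tempting, and the document does not support them:
- **That power is really 63%.** This requires p to be the Walsh-average probability. The article defines it through an after score and a before score, which is a different quantity.
- **That the pilot scores were certainly analysed as two independent samples.** The match shows which formula fits the sizes. It does not show how 0.329 and 0.217 were estimated.
- **That 90% is the power of intervention against control.** The article takes the effect from a pilot before-after change and mentions no pilot control group.

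**Conclusion.** The stated source of the sample sizes is wrong as written, in both strands. Assuming a two-sided test, 60 and 22 are rank-sum sizes, and the 90% appears to belong to a comparison of two independent samples. For the signed rank test the power at these sizes is undetermined. On the text's own definition of the probability it ranges from about 75% to 98% over the distributions tried, and it exceeds 99% if the scores were treated as independent but are positively correlated. The point is therefore a misnamed test and an unsupported power statement, with no demonstrated loss of power. It merits correction because it concerns the article's only power claim, on the primary outcome. The direction of the probability is a separate, smaller error that does not change the sizes.

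**What to change.** Revise the two sample size paragraphs in one of two ways:
- Name the two-sample rank-sum formula, two-sided 0.05, as the source of 60 and 22; or
- Keep the signed rank test, recompute its power at 60 and 22 from the pilot paired differences, and restate that figure.

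In either case:
- Say plainly that the effect is a pilot before-after change.
- Do not present 90% as the power of the intervention-versus-control comparison unless that effect is justified as a difference from control.
- Check the direction of the probability against the pilot data and correct it. If the label is simply reversed, the probability of a lower after score is 1 − 0.329 = 0.671 and 1 − 0.217 = 0.783.

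The cost is the rewording of two paragraphs and, for the second option, one calculation from the pilot data. The downside is that the restated power may be less favourable. Until it is recomputed, nobody can promise that the sizes will stand for the signed rank test.
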